### **7.3.12 Day 85 (+1), post-3rd vaccination, Visit 11 A, Scheduled home visit**

- Study personnel (field workers) will visit the subject at home to solicit local and systemic reactions and concomitant medication information.

- Any spontaneous AEs that have occurred since the last visit will be assessed.

### **7.3.13 Day 86 (+1), post-3rd vaccination, Visit 12**

- Subjects will be evaluated in the clinic 2 days after their third immunization. Vital signs (auxiliary temperature, blood pressure, pulse) will be taken, and information regarding systemic and local reactions will be solicited and recorded. An examination of the vaccination site will be performed.
- Any spontaneous AEs that have occurred since the last visit will be assessed.
- A PE will be performed, to include an assessment of lymph nodes, lungs, heart, liver, and spleen. A complete neurologic examination will also be performed, to include assessment of motor function, sensory function, and deep tendon reflexes.
- Obtain subject's interim medical history.
- Concomitant medications will be reviewed and updated, if applicable.
- Subjects will be reminded about the scheduled home visits during which field workers record their auxiliary temperatures, local and systemic reactions for the 14-day period after vaccination.
- Subjects will be reminded to come back to the study center if they develop any severe reactions (grade 3) during the study.

### **7.3.14 Day 91 (±2), post-3rd vaccination, Visit 13**

- Subjects will be evaluated in the clinic 7 days after their third immunization. Vital signs (auxiliary temperature, blood pressure, pulse) will be taken, and information regarding systemic and local reactions will be solicited and recorded. An examination of the vaccination site will be performed.
- Any spontaneous AEs that have occurred since the last visit will be assessed.
- A PE will be performed, to include an assessment of lymph nodes, lungs, heart, liver, and spleen. A complete neurologic examination will also be performed, to include assessment of motor function, sensory function, and deep tendon reflexes.
- Obtain subject's interim medical history.

- Concomitant medications will be reviewed and updated, if applicable.
- A 10-mL blood sample will be collected for safety laboratory (hematology, chemistry) testing. A urine sample will also be obtained for urinalysis .
- Subjects will be reminded about scheduled home visits during which field workers record their auxiliary temperatures, local and systemic symptoms for the 14-day period after vaccination.
- Subjects will be reminded to come back to the study center if they develop any severe (grade 3) reactions during the study.

#### **7.3.15 Day 98 ( $\pm 3$ ), post-3rd vaccination, Visit 14**

- Subjects will be evaluated in the clinic 14 days after their third immunization. Vital signs (auxiliary temperature, blood pressure, pulse) will be assessed and recorded. Information regarding local and systemic reactions will be solicited and recorded. An examination of the vaccination site will be performed.
- Any spontaneous AEs that have occurred since the last visit will be assessed.
- A targeted PE will be performed if indicated by the subject's interim medical history. A complete neurologic examination will also be performed, to include assessment of motor function, sensory function, and deep tendon reflexes.
- Concomitant medications will be reviewed and updated, if applicable.

#### **7.3.16 Day 112 ( $\pm 3$ ), post-3rd vaccination, Visit 15**

- Subjects will be evaluated in the clinic 28 days after their third immunization. Vital signs (auxiliary temperature, blood pressure, pulse) will be assessed and recorded. An examination of the vaccination site will be performed.
- Any spontaneous AEs that have occurred since the last visit will be assessed.
- A targeted PE will be performed if indicated by the subject's interim medical history. A complete neurologic examination will also be performed, to include assessment of motor function, sensory function, and deep tendon reflexes.
- Concomitant medications will be reviewed and updated, if applicable.
- A 50-mL blood sample will be collected for humoral and cell-mediated immune assays.

**7.3.17 Day 140 ( $\pm 1$  month), Visit 16**

- Subjects will be evaluated in the clinic. Vital signs (auxiliary temperature, blood pressure, pulse) will be assessed and recorded. Subjects will be interviewed regarding any potential risk behavior that would increase their chance of becoming infected with HIV virus.
- Any spontaneous AEs that have occurred since the last visit will be assessed.
- A targeted PE will be performed if indicated by the subject's interim medical history.
- Concomitant medications will be reviewed and updated, if applicable.
- A 50-mL blood sample will be collected for humoral and cell-mediated immune assays.

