#### **3.2.2 Secondary Outcome Measures**

- Antibody titers against the malaria circumsporozoite antigen at days 0, 28, 56, 84, 112 and 140 (Geometric Mean titer and individual log ELISA units).
- Neutralizing antibody titers against Adenovirus type 35 by Adenovirus Neutralization Assay at days 0, 28, 56, 84, 112 and 140 (GMT).

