### **7.3.5 Day 28 (window period: -3 days to +3 days), Visit 6, 2nd vaccination**

- Eligibility criteria will be reviewed with subjects. Vital signs (axillary temperature, blood pressure, pulse) and interim medical history will be obtained.
- Any spontaneous AEs that have occurred since the last visit will be assessed.
- A targeted PE will be performed if indicated by the subject's interim medical history. A complete neurologic examination will also be performed, to include assessment of motor function, sensory function, and deep tendon reflexes.
- Concomitant medications will be reviewed and updated, if applicable.
- A urine pregnancy test will be performed, and negative results, within 24 hours prior to vaccination, will be confirmed on all females of childbearing potential
- A 50-mL blood sample for humoral and cell-mediated immune assays will be collected from a vein in the arm prior to vaccination.
- A thick smear slide will be prepared from the 50ml blood sample and will be stored to be read for parasitemia at a later time if necessary. Refer to section 8.2.1.
- Enrolled subjects will receive Ad35.CS.01 vaccine or normal saline placebo control at the same dosage used on Day 0.
- Subjects will be observed in the clinic for a minimum of 30 minutes following vaccination. After 30 minutes, the vaccination site will be examined, vital signs will be obtained, and the subject will be questioned about the presence of any localized or systemic reactions.
- Subjects will be informed that a field worker will be visiting them at home during 14 days post each vaccination to record all medical information.
- Subjects will be instructed to come back to the study center if they feel febrile on any individual day or if they develop any severe reactions following vaccination.

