**7.3.7 Day 30 (+1), post-2nd vaccination, Visit 7**

- Subjects will be evaluated in the clinic 2 days after their second immunization. Vital signs (auxiliary temperature, blood pressure, pulse) will be taken, and information regarding systemic and local reactions will be solicited and recorded. An examination of the vaccination site will be performed
- Any spontaneous AEs that have occurred since the last visit will be assessed.
- A PE will be performed, to include an assessment of lymph nodes, lungs, heart, liver, and spleen. A complete neurologic examination will also be performed, to include assessment of motor function, sensory function, and deep tendon reflexes.
- Obtain subject's interim medical history.
- Concomitant medications will be reviewed and updated, if applicable.
- Subjects will be reminded about scheduled home visits during which field workers record their auxiliary temperatures, local and systemic reactions for the 14-day period after vaccination.
- Subjects will be reminded to come back to the study center if they develop any severe reactions during the study.

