### **8.2.2.1 Humoral Assays**

Ten mL of blood will be collected per draw for humoral assays at 6 time points: 1) day 0 prior to the 1st vaccination, 2) just prior to the 2nd vaccination, 3) 28 days after the 2nd vaccination, 4) just prior to the 3rd vaccination, and 5) 28 days after the 3rd vaccination, 6) 56 days after 3rd vaccination. The assays to be performed include an ELISA to determine antibody titers against the circumsporozoite antigen and an Adenovirus Neutralization Assay for neutralizing antibody titers against Adenovirus type 35, and possibly other relevant Adenovirus serotypes (e.g. Adenovirus type 5).

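### The ±1-month window for the Day 140 immunogenicity draw overlaps the Day 112 window, so two time points that are reported separately need not be separate in time

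*Protocol*

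**What the plan says.** Section 7.3.17 sets the visit at "Day 140 ( $\pm 1$ month), Visit 16" and orders the immunology draw there: "A 50-mL blood sample will be collected for humoral and cell-mediated immune assays". The preceding visit, which takes the same sample, is headed "Day 112 ( $\pm 3$ ), post-3 rd vaccination, Visit 15" (Section 7.3.16), and its text reads "Subjects will be evaluated in the clinic 28 days after their third immunization".

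Section 8.2.2.1 states the intended time of the last draw as "6) 56 days after 3 rd vaccination", and Section 8.2.2.2 gives the same six times for the cellular assays. Section 3.2.2 lists the circumsporozoite antibody outcome "at days 0, 28, 56, 84, 112 and 140 (Geometric Mean titer and individual log ELISA units". Sections 3.2.2 and 3.2.3 use the same days for the Ad35 neutralization and T-cell outcomes.

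The other scheduled post-baseline immunology draws (Days 28, 56, 84 and 112; Sections 7.3.5, 7.3.10, 7.3.11 and 7.3.16) all have ±3-day windows. The ±1-month window otherwise belongs to the follow-up visits at Days 196 and 252, which take no immunology sample.

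On the visits after doses 2 and 3: dose 2 is given at "Day 28 (window period: -3 days to +3 days), Visit 6", and dose 3 at Day 84 ±3. Visit 7, for instance, is headed Day 30 (+1), but its text reads "Subjects will be evaluated in the clinic 2 days after their second immunization".

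**The concern.** Days 112 and 140 are meant to be two points on the response curve after dose 3, at 28 and 56 days. The collection rule does not guarantee that. A site can comply fully and still draw a subject's Day 140 sample when the Day 112 sample is due, or almost three months after the dose. No section sets a minimum gap between the two draws.

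The study has 10 vaccinees and 2 placebo recipients per group (Section 4) and aims to describe how immune responses behave rather than to test hypotheses (Section 11.2). A GMT over 10 people whose times since dose 3 differ by up to about two months mixes a difference in response with a difference in timing. Recording actual dates helps, but no analysis can recover a 56-day value from blood drawn at 28 days.

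**Working it through.** **Nominal days.** Dose 3 is on Day 84. 84 + 28 = 112 and 84 + 56 = 140, so the nominal schedule is consistent with Section 8.2.2.1. The difficulty is in the windows.

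**Inputs.** Visit 15: 112 ±3 = Days 109-115 (Section 7.3.16). Dose 3: 84 ±3 = Days 81-87 (Section 7.3.11). Visit 16: 140 ± m, where m is one month (Section 7.3.17). The protocol does not define the length of a month, so I take m = 28, 30 and 31.

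**Overlap and time since dose 3.** Shared study days run from max(140 − m, 109) to min(140 + m, 115). Time since dose 3 runs from (140 − m) − 87 to (140 + m) − 81. If both visits are counted from dose 3 instead, Visit 15 is 28 ±3 = 25-31 days and Visit 16 is 56 ± m days.

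| m | Visit 16, study days | Shared with Days 109-115 | Days since dose 3 | Shared if both counted from dose 3 |
|---|---|---|---|---|
| 28 | 112-168 | 112-115 | 25-87 | 28-31 |
| 30 | 110-170 | 110-115 | 23-89 | 26-31 |
| 31 | 109-171 | 109-115 | 22-90 | 25-31 |

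The visits overlap in every row, on either way of counting. With m = 30 the end points are 110 − 87 = 23 and 170 − 81 = 89, against a nominal 56.

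**Illustration of size (assumption, not in the protocol).** Suppose titres fall exponentially with a half-life h of 30 to 60 days.
- Two samples at opposite ends of a 60-day window differ by 2^(60/h): 4-fold at h = 30 and 2-fold at h = 60. This is an extreme contrast between two subjects, not a bias in a GMT.
- If k of 10 vaccinees are sampled 28 days early (at 28 instead of 56 days), the group GMT is inflated by 2^(28k/(10h)). For k = 1 this is 1.07 at h = 30 and 1.03 at h = 60. For k = 5 it is 1.38 and 1.18.

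One stray sample matters little; a habit of early or late booking in one group matters.

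**Visits after doses 2 and 3.** If the study-day headings are taken literally and the dose moves ±3 days:
- Visit 7: 30 − 31 = −1 to 31 − 25 = 6 days after dose 2 (nominal 2).
- Visit 8, with safety laboratory tests: 33 − 31 = 2 to 37 − 25 = 12 days (nominal 7).
- Visit 10: 53 − 31 = 22 to 59 − 25 = 34 days (nominal 28).

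Dose 3 gives the same ranges for Visits 12, 13 and 15. If the visit text is followed, the ranges are 2-3, 5-9 and 25-31 days, and the dose window adds no drift.

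**The case against.** The best defence is that immunogenicity here is secondary or exploratory, descriptive and of pilot size (the sample size text and Section 11.2). Individual ELISA values are an outcome and cellular samples are labelled with the date, so time since dose can be used in the analysis, and a statistical analysis plan that is not shown may do so. There is no stated persistence objective. All of this limits the consequence. It does not remove the fault, which lies in a collection rule: sample times that need not differ cannot be separated afterwards.

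Four stronger readings are tempting, and the documents do not support them.
- **The Day 140 draw can precede the Day 112 window.** It cannot. With a 30-day month Visit 16 opens on Day 110, and even a 31-day month gives Day 109, the day Visit 15 opens.
- **Visits after doses 2 and 3 are tied to study day alone.** The text of Visits 7-10 and 12-15 counts from the immunization, and the headings of Visits 6A-10 and 11A-15 also label them as post-vaccination. What remains is two labels that are not reconciled.
- **Early reactions would be missed.** Subjects are observed for at least 30 minutes after each dose, and field workers visit on Days 1-14 after each vaccination except on clinic days (Section 7.2; Appendix A, footnote 5). These visits move with the dose. Only the timing of the clinic examinations and the Day 7 laboratory tests is exposed.
- **A Day 25 dose makes Visit 7 five to six days late.** On the literal headings the visit is 5-6 days after the dose, which is 3-4 days later than the intended 2.

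**Conclusion.** The point holds for Visit 16. Its window overlaps that of Visit 15 whatever the month length and whichever anchor is used, and the sample defined as 56 days after dose 3 may be taken about 23-89 days after it (30-day month, dose 3 on Days 81-87). This can blur the Day 140 GMT and T-cell estimates and their separation from Day 112. How far depends on how sites book the visit and how fast responses change; neither is known, and the half-lives above are assumptions. It is worth correcting, but it leaves the primary safety outcomes intact.

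The two anchors for Visits 6A-10 and 11A-15 are a minor wording inconsistency. Even on the literal study-day reading, the immunology draws at Visits 10 and 15 move only to 22-34 days against 28.

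**What to change.** Count the Visit 16 immunogenicity draw from the actual date of dose 3, with a window that cannot meet Visit 15. For example, 56 ±7 days gives 49-63 days after dose 3, against 25-31 for Visit 15, so the two draws are at least 49 − 31 = 18 days apart. The ±7 is one workable choice; any width that keeps the windows apart serves. Carry the change into Section 7.3.17, Appendix A and the eCRF window checks.

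Separately, reconcile the study-day labels in the headings and Appendix A with the post-immunization wording of the visit text for Visits 6A-10 and 11A-15. With one stated anchor, sites will not differ in when they do the clinic examinations and Day 7 safety laboratory tests.

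The cost is revised window wording and edit checks, less scheduling freedom at one visit, and probably a few more window deviations there.

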**7.3.18 Day 196 ( $\pm 1$  month), Visit 17**

- Subjects will be evaluated in the clinic. Vital signs (auxiliary temperature, blood pressure, pulse) will be assessed and recorded. Subjects will be interviewed regarding any potential risk behavior that would increase their chance of becoming infected with HIV virus.
- Any spontaneous AEs that have occurred since the last visit will be assessed.
- A targeted PE will be performed if indicated by the subject's interim medical history.
- Concomitant medications will be reviewed and updated, if applicable.

**7.3.19 Day 252 ( $\pm 1$  month), Visit 18**

- Subjects will be evaluated in the clinic. Vital signs (auxiliary temperature, blood pressure, pulse) will be assessed and recorded. Subjects will be interviewed regarding any potential risk behavior that would increase their chance of becoming infected with HIV virus.
- Any spontaneous AEs that have occurred since the last visit will be assessed.
- A targeted PE will be performed if indicated by the subject's interim medical history.
- Concomitant medications will be reviewed and updated, if applicable.

**7.3.20 Day 308 (+1 month), Visit 19**

- Subjects will be evaluated in the clinic. Vital signs (auxiliary temperature, blood pressure, pulse) will be assessed and recorded. Subjects will be interviewed regarding any potential risk behavior that would increase their chance of becoming infected with HIV virus.
- Any spontaneous AEs that have occurred since the last visit will be assessed.
- A targeted PE will be performed if indicated by the subject's interim medical history.
- Concomitant medications will be reviewed and updated, if applicable.

**7.3.21 Day 365 (+1 month), Visit 20**

- Subjects will be evaluated in the clinic. Vital signs (auxiliary temperature, blood pressure, pulse) will be assessed and recorded. Subjects will be interviewed regarding any potential risk behavior that would increase their chance of becoming infected with HIV virus.
- Any spontaneous AEs that have occurred since the last visit will be assessed.
- A targeted PE will be performed if indicated by the subject's interim medical history.
- Concomitant medications will be reviewed and updated, if applicable.
- A 5-mL blood sample will be collected for HIV testing.

**7.4 Early Termination**

Subjects may be discontinued from follow-up if any of the following criteria are met:

- Death
- Serious illness or disability making it impossible to maintain follow-up
- Lost to follow-up
- Subject choice
- Termination of the study

- Any circumstance in the opinion of the investigator that would prevent the subject from completing follow-up or that would put the subject at risk.

## 7.5 Early Termination Visit

If a subject is terminated from the study early, when applicable, every effort should be made to perform the following procedures:

- Review current health status and note any changes since the last visit.
- Record all concomitant medications.
- Obtain 10-mL blood sample for safety laboratory testing (hematology, chemistry).
- Obtain 50-mL blood sample for the humoral and cell-mediated immune assays.
- Obtain 5-mL blood sample for HIV testing.
- Obtain urine specimen for urinalysis.
- Perform a targeted physical examination, as indicated.
- Solicit information regarding AEs. Any ongoing related AEs will be followed to resolution or until a stable chronic condition has been established.
- Subjects will be encouraged to permit continued follow-up of AEs if possible.

## 7.6 Unscheduled Visit

Subjects may be asked to come in for additional clinic visits if the need arises for follow-up of local or systemic AE such as neurologic or febrile illnesses. Neurological symptoms will be evaluated with a full neurological exam and neurological consultation if needed. Any febrile illness will be evaluated as necessary to identify the etiology following standard procedures at the site.

A supplemental visit source document will be filled and signed by the appropriate personnel. All unscheduled visits will be entered into the EMMES Corporation AdvantageEDCSM internet data entry system on the appropriate eCRFs. Please see the Manual of Procedures for details.

## **8 STUDY PROCEDURES/EVALUATIONS**

### **8.1 Clinical Evaluations**

Medical history will be obtained by interview of the subjects. Subjects will be queried regarding a history of significant medical disorders of the head, eyes, ears, nose, throat, mouth, cardiovascular system, lungs, gastrointestinal tract, liver, pancreas, kidney, nervous system, blood, lymph glands, endocrine system, musculoskeletal system, skin, and genital/reproductive tract. A history of any allergies, cancer, immunodeficiency, psychiatric illness, substance abuse, and autoimmune disease will be solicited.

All current medications (prescription, over-the-counter drugs, vitamins, and supplements) will be recorded. Assessment of eligibility also will include a review of permitted and prohibited medications (per the inclusion/exclusion criteria).

A physical examination will be conducted to include an assessment of lymph nodes, lungs, liver, heart, and spleen. A full neurological examination will also be conducted. Axillary temperature, pulse and blood pressure will be determined before immunization.

A targeted PE will be conducted on routine visit dates. The extent of this PE will be based on any reported AEs or reactogenicity events or to follow up on previously reported AEs.

Solicited reactogenicity assessments will include a brief history for assessment of AEs and a targeted physical examination, which includes an assessment of erythema, induration, pain/tenderness, and ecchymosis at the injection site.

The subject will be interviewed about solicited local and systemic reactogenicity and spontaneous AEs, and the data transcribed into the case report form (CRF).

### **8.2 Laboratory Evaluations**

#### **8.2.1 Clinical Laboratory Evaluations**

- Hematology: hemoglobin (Hgb), white blood cell count (WBC) with machine differential, absolute neutrophil count (ANC), and platelet count (5 mL blood).
- Chemistry: glucose, electrolytes (sodium, potassium), alanine aminotransferase (ALT), aspartate aminotransferase (AST), and creatinine (5 mL blood).
- Serology: HIV, HBsAg, HCV antibodies, (10 mL blood).

- Urinalysis: dipstick for blood and protein and urine  $\beta$ -HCG prior to each vaccination.
- A thick smear slide will be prepared prior to each vaccination and will be stored to be read for parasitemia at a later time in the event that a safety concern arises regarding a possible association between vaccination and concomitant asymptomatic parasitemia.

## **8.2.2 Humoral and Cell-mediated Immune Assays**

To assess both humoral and cell-mediated immune responses to the vaccine, 50 mL of blood will be drawn from subjects on the following study days: 0, 28, 56, 84, 112, 140 days. From the 50 mL blood for immunological responses, 10mL will be used for serum isolation and subsequent humoral assays, and 40 mL blood will be used for cellular assays: 30mLs for PBMC isolation and 10 mL for whole blood stimulation followed by cytokine ELISA. Complete information on all immunological assays, including methods, reference standards, and performance sites are included in the Manual of Procedures.

